We design a randomized controlled functional brain imaging trial with a 10-week observation period, aiming at: (1) re-identifying the long-lasting effect of acupuncture treatment for FD by comparing the changes of therapeutic effect at three time points (the baseline vs. the end of treatment vs. the end of follow-up); (2) investigating the central mechanism of the long-lasting effect of acupuncture; and (3) exploring the influence of the *deqi* sensation on the long-lasting effect and its potential central mechanism.

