### Sample size

According to our previous study, Nepean Dyspepsia Index (NDI) scores of FD patients decreased by 12.2 points after acupuncture and by 7.8 points after sham acupuncture [23]. In this study, we anticipated a reduction of NDI score by 12 points after acupuncture with the *deqi* sensation and a reduction by 8 points after acupuncture without the *deqi* sensation, and we anticipated a reduction by 4 points in the wait-list control due to regression to the mean effect. With *α* = 0.05, 1 − *β* = 0.8, and a standard deviation of 10, we needed at least 96 participants in total. Considering a dropout rate of 10%, a total of 105 participants will be included in this trial. According to the sample size of previous blood-oxygenation-level-dependent fMRI (BOLD-fMRI) studies, 20 subjects is the reasonable sample size with stable statistical effect [24, 25]. Considering the dropout rate and loss of data due to head motion during fMRI scans, 25 participants from each group will receive fMRI scans in this study.

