## Data analysis

### Clinical data analysis

The intention-to-treat analysis will be used for all allocated participants in the baseline. This study focuses on the lasting-effect of acupuncture, and the observed data will be used as the primary analysis and last observation-carried-forward (LOCF) analysis will be taken as a sensitivity analysis. Clinical outcome will be analyzed using SPSS 22.0 statistics software (IBM SPSS Statistics, IBM Corp, Somers, NY, USA). Data on Skewed distribution will be normalized. Means, standard deviations, and 95% confidence intervals (CIs) will be used to describe the continuous data.

The demographic and baseline characteristics among three groups will be compared using one-way analysis of variance (ANOVA). A *χ*^2^ test will be used for categorical variables. Due to the occurrence of self-healing tendency in FD, it is important to testify the existence of acupuncture effect. The clinical outcome NDI and SF-LDQ scores will be compared between the acupuncture group and the wait-list group among three time points by using the repeated measures ANOVA (two independent groups with repeated measures). Then, the acupuncture group with and without *deqi* at three time points will be primarily compared using repeated measures model.

A two-sided test will be used during the analysis, with a significance level of 0.05. The data will be analyzed by statisticians who are blinded to the test settings.

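### The primary repeated measures comparison treats baseline as an outcome level and names no end-of-follow-up contrast, so neither of its overall terms tests the long-lasting effect

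*Protocol article*

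**What the plan says.** The Background section defines the long-lasting effect as benefit still perceived for a time after treatment has stopped. The first aim is "re-identifying the long-lasting effect of acupuncture treatment for FD by comparing the changes of therapeutic effect at three time points", and these are baseline, end of treatment and end of follow-up. The third aim asks how deqi influences that effect. The Clinical data analysis section repeats that the lasting effect is the study's focus.

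The same section then sets two comparisons. NDI and SF-LDQ are compared between acupuncture and wait-list "by using the repeated measures ANOVA (two independent groups with repeated measures"). After that, the arms with and without deqi "at three time points will be primarily compared using repeated measures model". On error control it says: "A two-sided test will be used during the analysis, with a significance level of 0.05". It does not say which term of the model is tested, names no between-arm difference at the end of follow-up, and gives baseline no role as a covariate. The Outcome assessments section confirms that baseline is one of the three assessments.

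**The concern.** A repeated measures analysis over baseline, end of treatment and end of follow-up gives two overall between-arm tests. The group main effect compares the arms on the average of all three visits. Randomisation makes the expected baseline difference zero, so that visit only dilutes the effect. The group-by-time interaction asks whether the arms' profiles differ anywhere, and a difference confined to the end of treatment is enough to make it significant. The trial asks something narrower: do the arms still differ four weeks after the last session?

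At stake is the headline claim. If the stated model is read through its overall terms, a significant result would fit a lasting benefit and a vanished one equally well. With no term or contrast fixed in advance, the choice among main effect, interaction and visit-wise comparisons could be made after the data are seen.

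**Working it through.** **Inputs from the Sample size section.** The plan assumes "a reduction of NDI score by 12 points after acupuncture with the" deqi sensation, "a reduction by 8 points after acupuncture without the" sensation, and "a reduction by 4 points in the wait-list control due to regression to the mean effect". The between-arm differences are therefore 12 − 8 = 4 points (with versus without deqi) and 12 − 4 = 8 points (deqi versus wait-list). The section also gives power "0.8, and a standard deviation of 10, we needed at least 96 participants in total", that is 32 per arm. Alpha is 0.05, two-sided.

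**Assumptions, because the article gives no figure.** Compound symmetry with score variance s² and within-patient correlation rho of 0.3 to 0.7. SD 10 is read first as the SD of change, so 2s²(1 − rho) = 100 and s²(1 − rho) = 50.

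**The plan's own figure.** A one-way ANOVA on change with means 12, 8 and 4 has noncentrality 32 × (4² + 0² + 4²)/100 = 10.24, which gives 81.2% power. With 31 per arm the power is 79.8%. The stated 96 is reproduced.

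**Group-by-time test (2 and 124 df).** Noncentrality = (n/2) × (sum of squared deviations of the arm differences from their mean over visits) / [s²(1 − rho)].
- Vanished benefit (0, d, 0): the deviations are −d/3, 2d/3, −d/3, and their squares sum to 2d²/3.
- Sustained benefit (0, d, d): the deviations are −2d/3, d/3, d/3, and their squares also sum to 2d²/3.
- d = 4: 16 × 10.67/50 = 3.41, rejection in 35% of trials under either profile.
- d = 8: 16 × 42.67/50 = 13.65, rejection in 92% under either profile.

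Under compound symmetry the test therefore has identical power for the two profiles, whatever the sample size or rho. Simulation with 10,000 runs agreed (for the vanished profile at rho 0.5, 36% for 4 points and 91% for 8). A comparison of change from baseline to follow-up rejected in about 5% under the vanished profile.

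**Group main effect (1 and 62 df).** A sustained 4-point difference averages (0 + 4 + 4)/3 = 2.67. The variance of a patient's three-visit mean is s²(1 + 2rho)/3. At rho 0.5, s² = 100 and this variance is 66.7, so noncentrality is 16 × 2.67²/66.7 = 1.71 and power is 25%. At rho 0.3 and 0.7 power is 40% and 15%.

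**Baseline-adjusted difference at follow-up (1 and 61 df).** The residual variance is s²(1 − rho²) = 50(1 + rho), and noncentrality for 4 points is 16 × 16/[50(1 + rho)].

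| rho | noncentrality | power, adjusted follow-up contrast | power, group-by-time |
|---|---|---|---|
| 0.3 | 256/65 = 3.94 | 50% | 35% |
| 0.5 | 256/75 = 3.41 | 44% | 35% |
| 0.7 | 256/85 = 3.01 | 40% | 35% |

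For a vanished benefit the adjusted contrast rejects in 5%. An unadjusted comparison of change from baseline to follow-up has noncentrality 256/100 = 2.56 and power 35%, the same as the interaction.

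**Other reading of SD 10.** The article does not say whether SD 10 refers to the score or to the change. As the SD of the score at rho 0.7, s²(1 − rho) = 30. The 4-point interaction then rejects in 55% of trials under either profile, and the adjusted follow-up contrast has 60% power for a sustained benefit. At rho 0.5 the two readings coincide.

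**The case against.** The strongest reply is that the article fixes less than the concern needs. For the deqi comparison it says only that a repeated measures model is used. It does not declare the main effect or the interaction decisive, and such a model can yield an arm contrast of change from baseline to follow-up. The choice of contrast is something an article may leave to an analysis plan. This stands in part: a reader might infer that the trial will call a vanished benefit lasting, and the document does not say so. What remains is that the article does state its primary comparison, states it over three levels with baseline among them, and does not tie it to the time point that carries the question.

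Three further limits stand.
- The 92% belongs to deqi versus wait-list. For the comparison called primary, the figure is about 35%.
- Neither figure is a type I error rate. When a benefit is transient the profiles do differ, so the interaction is right to reject. The error would lie in reading that result as persistence. The planned means, SDs and confidence intervals, if given by visit, would show that the benefit had gone. Looking at means is still not a pre-specified test.
- It is tempting to say that including baseline wastes much power. Against a follow-up test the gain is modest and comes from baseline adjustment: the unadjusted change test only matches the interaction. If SD 10 is the SD of the score, the gain is gone by a correlation of about 0.84. Averaging the two post-baseline visits is no remedy either, because a vanished 8-point benefit averages to 4 points, exactly like a sustained 4-point one.

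**Conclusion.** The point holds as a mismatch between question and test. The article defines its target as benefit after treatment stops, then sets a primary comparison whose overall terms either dilute that benefit (4 points to 2.67) or cannot separate it from one that has disappeared. For a vanished benefit the group-by-time test is significant in about 35% of trials at 4 points and about 92% at 8 points, against 5% for a follow-up contrast. These percentages assume 32 per arm, change SD 10 and compound symmetry. That the interaction can be significant without any follow-up difference does not depend on the correlation.

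The power argument is secondary. The correlation is not given, and the gain over the interaction is 5 to 15 percentage points for rho 0.7 down to 0.3. The documents do not support saying that the planned analysis is invalid or that it has an inflated false-positive rate. This is a worthwhile improvement at almost no cost, not a fault that must be cured before the trial can be interpreted.

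**What to change.** Restate the primary analysis as a mixed model on NDI at the two post-baseline visits, with baseline NDI as covariate and terms for arm, visit and arm-by-visit. Name the adjusted difference between the arms with and without deqi at the end of follow-up as the test of the long-lasting effect. Report the adjusted end-of-treatment difference beside it and state that the two are read together: a difference at both visits supports persistence, while one at follow-up alone suggests late onset. Use the same model for acupuncture versus wait-list.

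The cost is a few sentences in the protocol or analysis plan. Baseline NDI is already collected, SPSS can fit the model, and no new data are needed. The Trial status section describes recruitment as still open, so the change could be dated before the analysis. It does not cure the low power for a 4-point difference (44% at rho 0.5 with 32 per arm), which is a separate matter.

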### fMRI data analysis

The fMRI scan data will be preprocessed and analyzed by SPM12 software (SPM12, Wellcome Department of Imaging Neuroscience, London, UK; http://www.fil.ion.ucl.ac.uk/spm/) performing on MATLAB 8.6 (Mathworks, Inc., Natick, MA, USA). After data preprocessing, regional homogeneity (ReHo), amplitude of low-frequency fluctuation (ALFF) and functional connectivity (FC) will be used to investigate the different cerebral responses between *deqi* and without *deqi*. Then correlation analysis will be conducted between clinical data and fMRI image data.

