**Methods:**

A randomized controlled functional brain imaging trial is currently being conducted in Sichuan, China. In total 105 functional dyspepsia (FD) patients will be allocated into three groups: an acupuncture with *deqi* group, an acupuncture without *deqi* group, and a wait-list group. This trial will include a 2-week baseline period, a 4-week treatment period, and a 4-week follow-up period. During the 4-week treatment, patients in two acupuncture groups will receive 20 sessions of acupuncture treatment with or without *deqi*. The Nepean Dyspepsia Index (NDI) and the short form Leeds Dyspepsia Questionnaire (SF-LDQ) will be used to evaluate the clinical efficacy of acupuncture treatment at baseline, the end of treatment, and the end of the follow-up. Functional magnetic resonance imaging (fMRI) scans will be performed to detect cerebral functional changes in 25 patients in each group at three time points mentioned above. The clinical data and fMRI data will be analyzed, respectively. Correlation analysis will be conducted to investigate the relationship between cerebral functional changes and symptom improvement.

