### Control

To investigate the influence of the *deqi* sensation on the long-lasting acupuncture effect, we choose acupuncture without *deqi* as the control group. In addition, to avoid the influence of a self-healing tendency, we design a wait-list group in which FD patients will not receive acupuncture treatment.

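### The fMRI analysis gives the scanned wait-list arm no stated role, so the planned brain–symptom correlation cannot by itself separate a mechanism of acupuncture's lasting effect from arm differences or self-healing

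*Protocol article*

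**What the plan says.** All statements are in the protocol article.

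- **Aims (end of Background).** Aim 2 is "investigating the central mechanism of the long-lasting effect of acupuncture". Aim 3 concerns the influence of deqi on that effect and its central basis.
- **fMRI data analysis.** Three brain measures (ReHo, ALFF and functional connectivity) "will be used to investigate the different cerebral responses between *deqi* and without *deqi". The next sentence is "Then correlation analysis will be conducted between clinical data and fMRI image data". No pooling rule, covariate or comparator is given.
- **Abstract, Methods.** The purpose of that step is stated: "Correlation analysis will be conducted to investigate the relationship between cerebral functional changes and symptom improvement".
- **Needle sensation evaluations.** A second fMRI comparison regroups the needled patients by reported sensation. It also leaves out the wait-list.
- **Sample size.** "25 participants from each group will receive fMRI scans in this study", so wait-list patients are scanned. Study design sets the scans at baseline, end of treatment and end of follow-up. For the untreated arm, "we anticipated a reduction by 4 points in the wait-list control due to regression to the mean effect".
- **Control.** The reason for the third arm: "to avoid the influence of a self-healing tendency, we design a wait-list group".
- **Clinical data analysis.** "Due to the occurrence of self-healing tendency in FD, it is important to testify the existence of acupuncture effect". The contrast with the wait-list is then specified for the NDI and SF-LDQ scores only.

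**The concern.** The article names self-healing as the rival explanation and adds an arm to deal with it. It uses that arm for symptoms and scans it three times, but both fMRI comparisons it names are confined to needled patients. The correlation, the one step that joins brain to benefit, has no stated comparator.

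A correlation across patients tests whether two changes go together. The aims ask whether a brain change carries the lasting effect of acupuncture. The first can be true without the second in two ways, depending on how the arms are handled:

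- **Arms pooled without adjustment.** If both NDI and the brain measure differ by arm, arm membership alone produces a correlation.
- **Arms taken singly.** A brain measure that follows symptoms whatever the cause will correlate with NDI in needled arms too. Significance in one arm and not the other could be taken as specific to deqi.

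Correlating changes over the same interval also leaves open whether brain change comes before maintained relief or follows it. At stake is the mechanism conclusion, not the clinical comparison.

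**Working it through.** **Inputs.** From Sample size: NDI falls of 12, 8 and 4 points, SD 10, 25 scanned per arm, 20 taken as adequate. From Clinical data analysis: two-sided 0.05. The article gives no brain-change shifts and no brain–symptom correlations; those below are assumptions, shown as ranges. Simulations used 20,000 runs per setting unless noted.

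**1. The plan's own figure.** The article gives no figure for the correlation, only for the trial. f = √{[(12−8)² + 0² + (4−8)²]/3}/10 = √(32/3)/10 = 0.327. A three-group ANOVA then has power 0.812 with 32 per arm (96 in total) and 0.798 with 31. The stated 96 reproduces, so its inputs are used below.

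**2. Arms pooled, no link within any arm.** In SD units the NDI falls are 1.2/0.8/0.4. The correlation created by arm means is

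r = C / √[(1 + V_NDI)(1 + V_brain)],

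where C and V are the covariance and variances of the arm means. With z = artanh(r), the rejection rate is about Φ(z√(N−3) − 1.96) + Φ(−z√(N−3) − 1.96).

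- Three arms, brain shift 2/1/0 SD, 25 per arm: C = (0.4 + 0 + 0.4)/3 = 0.267; V_NDI = 0.32/3 = 0.107; V_brain = 2/3 = 0.667; r = 0.267/√(1.107 × 1.667) = 0.196; z√72 = 1.69; rejection about 39%.
- Two needled arms, brain shift 0.4 SD (equal to the NDI step), 25 per arm: r = 0.04/1.04 = 0.038; z√47 = 0.26; rejection about 5.8%.

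Simulation agrees:

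| Arms pooled | Assumed brain shift, SD | Rejection, 20–25 per arm |
|---|---|---|
| three | 0.5/0.25/0 | 7–8% |
| three | 0.8/0.4/0 | 12–13% |
| three | 1/0/0 or 1/0.5/0 | 14–17% |
| three | 2/1/0 | 33–40% |
| needled only | 0.4 | about 6% |
| needled only | 0.8 | about 8% |
| needled only | 1 | 8–9% |

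For the needled pair, 1.2 SD gives about 10–11%. After adjustment for arm, every setting returns to about 5%.

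**3. Arms taken singly.** With no link within the arm, rejection is 4.9–5.3%, so arm differences do no harm here. Now assume the same correlation in all three arms, wait-list included. With p the rejection rate in one arm, exactly one of the two needled arms is significant with probability 2p(1−p).

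| Correlation | p, n = 20 | exactly one | p, n = 25 | exactly one |
|---|---|---|---|---|
| 0.3 | 0.26 | 0.38 | 0.31 | 0.43 |
| 0.4 | 0.43 | 0.49 | 0.53 | 0.50 |
| 0.5 | 0.64 | 0.46 | 0.75 | 0.38 |

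A direct test of the difference between two arms' correlations (Fisher z) rejects in about 5%, as it should.

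**4. What arm adjustment does not do.** Under shared remission with no acupuncture effect (three arms, 25 each), the arm-adjusted correlation is still significant in 40%, 74% and nearly 100% of runs for correlations of 0.2, 0.3 and 0.5. It removes arm differences but not symptom tracking.

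**5. What a real mediator looks like.** Suppose brain change shifts by 1/0.5/0 or 2/1/0 SD and drives NDI with one common slope of 0.3 to 0.5. The arm × brain-change term is then significant in about 5% of runs (4,000 runs per setting), its nominal level, and the common slope in 63% to over 99%. The evidence lies in the arm difference in brain change together with the slope.

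**6. Power for a difference in correlation, 0.5 against 0.** One needled arm against wait-list, 25 each: 0.549/√(2/22) = 1.82, power about 45%; with 20 each, 36%. Both needled arms combined against wait-list: 47–57%.

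**The case against.** The strongest reply is that this is a condensed article. Coefficient, pooling and covariates may sit in the full protocol or analysis plan, and an arm-adjusted partial correlation would fit the present text. That stands, so no error rate can be attributed to the plan as such. What the article does fix is the pair of conditions it compares on brain measures, and the wait-list is not among them.

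A reader might infer stronger things that the documents do not support:

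- **That the correlation will reject for arm differences.** This needs pooling, which is not stated. Within one arm it cannot happen, and for the two needled arms at the protocol's own step size the excess is negligible.
- **That the plan treats a significant correlation as proof of mechanism.** The abstract promises only a relationship, and the aims speak of investigating and exploring.
- **That the 4-point fall in the wait-list itself creates a correlation.** A mean fall does not. Patients within the arm must also vary together on both measures, and the 0.3 to 0.5 used here is assumed.
- **That a mechanism requires the association to differ between arms.** It does not: step 5 shows that such a rule would miss a true mediator with a common slope about 95% of the time.

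**Conclusion.** The concern holds in limited form. The article gives the wait-list scans no role in the brain analysis, and its only brain–symptom step supports an association, not a mechanism of acupuncture's lasting effect. How far it could mislead depends on unstated handling of the arms and on assumed effects. The exposure is material if three arms are pooled unadjusted, small if only the needled arms are pooled, and a matter of misread single-arm significance if arms are analysed separately. The clinical NDI and SF-LDQ comparisons are unaffected. The text should be changed, since the data needed are already being collected.

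**What to change.** Amend the fMRI data analysis section as follows.

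1. Include the wait-list in the between-arm comparison of brain change.
2. Estimate the brain–symptom association in one model on all scanned patients, adjusted for randomised arm and baseline NDI.
3. Base any statement that the association differs between arms, such as a deqi-specific one, on a direct test of that difference and not on significance in one arm.
4. For the lasting effect, relate brain change from baseline to end of treatment to NDI at end of follow-up, adjusted for arm and end-of-treatment NDI.
5. Report a slope alone as an association. Read it as a possible mechanism only together with a randomised needled-versus-wait-list difference in brain change, under stated mediation assumptions.

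Do not make an arm × brain-change interaction a requirement for a mechanism, and do not present an arm-adjusted partial correlation as equivalent to the interaction model; they answer different questions.

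No new patients or scans are needed. The cost is slightly more analysis, low power for differences in association at 20 to 25 per arm, and possibly a weaker mechanism conclusion.

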## Discussion

Based on ancient records and recent RCT results, acupuncture has a long-lasting effect for treating dyspepsia, but its central mechanism and influential factors remain uncertain. Considering the importance of the *deqi* sensation for the acupuncture effect, we have designed a randomized controlled fMRI trial to explore the central mechanism of the acupuncture long-lasting effect and the influence of the *deqi* sensation on the long-lasting effect for the first time.

